## Background

Approximately one fourth of adults worldwide have chronic obstructive pulmonary disease (COPD) [1], and half of them suffer from insomnia [2] (difficulty falling or staying asleep, or poor-quality sleep that interferes with daytime functioning [3]). Insomnia is related to greater mortality [4–6], with studies showing *four times the mortality risk* for sleep times below 300 min [5, 6]. Insomnia also produces morbidity – insomnia sufferers generate 75 % greater healthcare costs than individuals without insomnia [7]. Lost productivity from insomnia is estimated at US$63.2 billion annually in the US alone [8]. People with COPD experience debilitating fatigue and a gradual decline in function that are partly related to insomnia [9–11]. However, insomnia medications are used with caution in COPD due to potential respiratory effects, hypoxia and effects on cognition [12]. Common features of COPD, such as dyspnea, chronic inflammation and emotional arousal (anxiety and depression), also affect insomnia and can interfere with therapy outcomes. Cognitive behavioral therapy for insomnia (CBT-I), a therapy that provides guidance on changing unhelpful sleep-related beliefs and behavior, is a promising non-pharmacological treatment that has demonstrated effectiveness for insomnia, but the efficacy of components and mechanisms of action of CBT-I have not been thoroughly examined in people with insomnia coexisting with COPD.

Insomnia is prevalent in people with medical disorders, and therapy for insomnia might improve these medical disorders [13]. However, there are only a limited number of randomized, controlled studies in this area. Although evidence obtained from studies that included participants with cancer [14, 15], renal failure [16], chronic pain [17], osteoarthritis, [18] and COPD [19, 20] support the notion that CBT-I is effective in reducing insomnia when coexisting with chronic illness, no studies to date have examined CBT-I specifically for people with COPD. It is yet undetermined whether improving self-efficacy for the medical illness (i.e., COPD) mediates outcomes after CBT-I, but our preliminary data suggest that education on COPD topics, such as management of dyspnea and COPD exacerbations, may improve self-efficacy and reduce depression, indirectly reducing insomnia and fatigue [20].

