#### Clinical assessment

The Health Report is used to monitor health status during the intervention and the follow-up period. We monitor COPD exacerbations and the use of corticosteroids, using procedures established for a previous study (NR08037). The Health Report Form is a two-page form that is easy to complete in 1 min or less. It includes the Epworth Sleepiness Scale [58] (ESS), which is used to assess daytime sleepiness in the CBT-I group during the intervention period. These data may be tested as covariates in the analyses.

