## Methods: data collection, data management and analysis

### Data collection

Screening procedures include an initial telephone screening to determine eligibility. Potential subjects are then scheduled for their first screening visit, which takes place at the CNSHR. At that visit, after informed consent is obtained, PFTs are performed, followed by questionnaires. Reliability and validity of pulmonary function testing have been previously demonstrated [62, 63]. The Hospital Anxiety and Depression Scale (HADS) [64] is administered to screen for major depressive symptoms. The HADS was designed for outpatients with medical illnesses, and it has been widely used in people with COPD [65–67]. Reliability and validity were demonstrated [68]. A cutoff score of 11 on the HADS depression subscale is used for depression [64]. A clinical questionnaire is completed at this visit to characterize the sample in terms of demographics and health history. Blood specimens are sent to Quest Diagnostics® for measurement of C-reactive protein and ferritin level. These tests are done in order to rule out anemia and to adequately describe the sample and may be used as covariates in the analyses.

The screening includes a one-night sleep study at home or at the UIC Sleep Science Center or the Hines VA Sleep Laboratory. The sleep study is used to screen potential subjects for sleep apnea, and low SaO_2_ during the night. Objective evidence of any primary sleep disorder according to standard clinical criteria is used to exclude subjects. The remaining subjects receive instructions for continued actigraphy monitoring by wearing an actigraph on their non-dominant wrist at home for a total of 1 week. They are instructed on how to complete the daily sleep diary.

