### Statistical analysis

#### Test of specific hypotheses

Descriptive statistics (means, standard deviation, frequency) and plots are used to screen the data prior to our main analyses. Necessary transformation and imputations are conducted based on the raw data distribution. Baseline adjustment for covariates (e.g., age, COPD severity (PFT), and gender) will be incorporated into the main effect analyses to reduce error variance and improve statistical power [69]. Data analyses is performed using SAS 9.3 statistical software (SAS Inc., Cary, NC, USA) and Mplus 6.0 (Muthén & Muthén, Los Angeles, CA, USA). All tests will be two-sided and an error rate of *α* <0.05 will be considered statistically significant. The test of each specific aim is described below, and all statistical analysis will employ an intent-to-treat approach. A fully specified statistical analysis plan will be written before unmasking.

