Aim 1: to determine the efficacy of individual treatment components, CBT-I and COPD-ED, on insomnia and fatigue. In this 2 × 2 design, participants are randomized into four groups created by crossing the two factors, CBT-I versus AC1 and COPD-ED versus AC2 (see Table 3). We hypothesize that both components will improve insomnia and decrease fatigue following the six-session program, and that participants will maintain these gains at 3 months post intervention. Our factorial design permits the test of an interaction between the two treatment components, and we will assess for the presence of a strong interaction effect. However, we do not anticipate a strong synergy of the treatments since our pilot work showed that both had within-group improvement, and the hypothesized mechanisms for change differ. If the interaction is negligible, we will proceed with the interpretation of averaged main effects as shown in Table 3. The statistical tests for both components will be more robust than tests against a simple control condition because they are averaged across the levels of the other treatment. That is, the effect of each component will be tested controlling for the effect of the other. This is an efficient design because all subjects will be used to test both components. Finally, it may be more acceptable to participants since all receive supportive contact and only one out of four conditions does not receive a component hypothesized as an active treatment for insomnia in COPD patients. We will employ mixed-effects models using insomnia and fatigue as time-varying dependent variables and treatment groups as fixed effects. Demographic and clinical characteristics will be entered as time-invariant covariates if baseline group differences are observed despite randomization. Individuals’ baseline sleep measures and change over time (i.e., intercept and slope) will be modeled as random effects. The null hypothesis will be rejected if a significant treatment × time interaction is observed. For example, a significant CBT-I × time effect in the hypothesized direction would mean that participants receiving CBT-I improved more than those who did not, averaged across the other conditions. The mixed models will be run using PROC MIXED SAS 9.3 (SAS Inc., Cary, NC, USA) and estimated by residual maximum likelihood (REML). Covariance pattern structures (compound symmetry and unstructured) will also be examined, and models will be compared using likelihood ratio tests or Akaike’s Information Criteria (AIC) which is a function of the log likelihood and can be compared across models.

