
**Table 3 Tab3:** Study design

Study design	CBT-I	AC1	Main effect COPD-ED
COPD-ED	35	35	70
AC2	35	35	70
Main effect CBT-I	70	70	

*AC1* attention control 1, *AC2* attention control 2, *CBT-I* cognitive behavioral therapy for insomnia, *COPD-ED* COPD education

Aim 2: to define the mechanistic contributors to the outcomes after CBT-I and COPD-ED. We hypothesize that CBT-I and COPD-ED components impact insomnia and fatigue through complementary mechanisms. We have previously shown that CBT-I was related to beliefs about sleep, sleep habits, self-efficacy for sleep, and that COPD-ED was related to management of COPD and emotional arousal, thus making them both appropriate candidates for an insomnia treatment approach for COPD patients. We will employ path analysis to test the conceptual model illustrated in Fig. 1 [70]. The model will test whether each treatment component is related to change in the hypothesized mediator, and whether that change is associated with improvement in the outcome. Direct and indirect treatment effects will be estimated. We will conduct path analyses as follows: (1) specification, (2) identification, (3) estimation, (4) testing of fit, and (5) respecification [71]. Potential moderators suggested by our previous work include gender, initial insomnia and fatigue severity, and inflammation and will be tested as interactions of the effect of each treatment component on the outcomes. Variables found to be a significant moderator of treatment will be tested further to determine if the effect is due to a moderated impact on significant mediator variables. Path models assume that variables used to describe relationships are manifest variables and measured without error. While we recognize that it would be preferable to estimate a measurement model, the feasible sample size for this study precludes more complex modeling. Thus, we acknowledge this limitation and will restrict path analysis to reliably measured variables, that is, with internal consistency of 0.80 or higher. Mplus (version 6) will be used to estimate the path models. The root-mean-square error of approximation (RMSEA) and Bentler’s Comparative Fit Index (CFI) will be reviewed to assess model fit. An adequate fit of the data to the model is indicated by a RMSEA value less than 0.08 and a CFI greater than 0.90.

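### Aim 2 reads a mediator–outcome association as mechanism without committing any baseline adjustment to that path, which randomisation does not protect

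*Protocol article*

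**What the plan says.** All references are to the protocol article.

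- **Purpose of Aim 2** (Test of specific hypotheses): "to define the mechanistic contributors to the outcomes after CBT-I and COPD-ED". The path model asks whether each component is related to change in the hypothesised mediator "and whether that change is associated with improvement in the outcome". It then states: "Direct and indirect treatment effects will be estimated".
- **Causal intent** (Trial design): mediators are also measured after the fourth session, to strengthen the test of a causal mediating effect.
- **Firm baseline adjustment** (Test of specific hypotheses, opening paragraph): covariates such as age, COPD severity and gender "will be incorporated into the main effect analyses to reduce error variance and improve statistical power".
- **Further covariates under Aim 1**: demographic and clinical characteristics "will be entered as time-invariant covariates if baseline group differences are observed despite randomization".
- **Optional covariates**: C-reactive protein and ferritin "may be used as covariates in the analyses" (Data collection). For the Health Report, "These data may be tested as covariates in the analyses" (Clinical assessment).
- **Possible shared causes** (Background): "Common features of COPD, such as dyspnea, chronic inflammation and emotional arousal (anxiety and depression), also affect insomnia and can interfere with therapy outcomes".
- **Limitation conceded for the path models** (Aim 2): variables are assumed to be measured without error. Mediator–outcome confounding is not mentioned.
- **Size of the path models** (Power analysis): 7–14 parameters, at 10 to 20 cases per parameter.

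**The concern.** Participants are randomised to components, not to mediator values. Someone whose disease is easier to live with may gain confidence, mood and sleep together, without the first two causing the third. That shared movement enters the mediator-to-outcome coefficient and, multiplied by a genuine component-to-mediator effect, is reported as an indirect effect.

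The adjustment rules that the protocol does state serve other purposes. One is for precision in the main effects. The other is triggered by imbalance between groups, yet a confounder that is perfectly balanced across the four arms still biases the mediator-to-outcome path. The fourth-session measurement helps with temporal order but does not remove shared causes. Testing moderators as treatment interactions does not adjust this path either.

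What is at stake is the product of Aim 2. The Discussion says that components found to be important can be included in new therapies, so a mechanism declared in error could shape what is built next.

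**Working it through.** **1. The protocol's own figure.** 140/20 = 7 and 140/10 = 14, so the range of 7–14 parameters reproduces.

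**2. Parameters in a single-mediator model.** Two component-to-mediator slopes + two component-to-outcome slopes + one mediator-to-outcome slope + two residual variances = 7.

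**3. Shared-cause simulation.** From the protocol: 35 per cell, N = 140, two-sided 0.05. Assumed: a component moves the mediator by 0.5 SD and the outcome by 0.5 SD, the true mediator-to-outcome effect is 0, and shared causes give a residual correlation ρ. The models are M ~ A + B and Y ~ A + B + M (A and B are the two components). Mediation is declared when both the A-to-M and the M-to-Y tests reach p < 0.05. There were 4,000 replicates per setting.

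With unit residual variances the M-to-Y slope tends to ρ, so the spurious indirect effect tends to 0.5 × ρ. As a share of the assumed total effect that is 0.5ρ/0.5 = ρ.

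| ρ | Spurious indirect effect (SD) | Share of total effect | False mediation, unadjusted | Half of the shared cause adjusted | All of it adjusted |
|---|---|---|---|---|---|
| 0 | 0 | 0% | about 4% | about 4% | about 4% |
| 0.1 | 0.05 | 10% | about 18% | about 8% | 3–5% |
| 0.2 | 0.10 | 20% | about 55% | about 22% | 3–5% |
| 0.3 | 0.15 | 30% | about 80% | 47–49% | 3–5% |

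Repeat runs agreed within about two percentage points. As a check, the power of the A-to-M test is about 0.836. The M-to-Y test alone rejects in about 0.228, 0.644 and 0.948 of trials, and the products are 0.19, 0.54 and 0.79. The unadjusted rate cannot exceed the A-to-M power of about 0.84.

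**4. Change on change, with no shared cause acting after baseline.** Let the baseline mediator and outcome correlate at r, and let each measure have pre-to-post correlation k. The two changes then correlate at r(1 − k)²/[2(1 − k)] = r(1 − k)/2. With k = 0.5 assumed, r = 0.3 gives 0.075 and r = 0.5 gives 0.125. False mediation is then roughly 11% to 27%. Adding both baselines to both equations returns it to about 5%. With k = 0.7 the unadjusted range falls to about 8–14%, so this part depends on how stable the measures are.

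**5. What a just-significant path represents.** With 136 residual degrees of freedom the critical t is 1.98. The matching residual correlation is 1.98/√(1.98² + 136) = 0.17. Shared causes producing a correlation of that size would fully account for a borderline finding.

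**6. Room for adjustment.** Three baseline covariates in both equations: 7 + 3 × 2 = 13 parameters, or 140/13 = 10.8 cases per parameter, within the protocol's convention. Nine covariates would give 7 + 18 = 25, or 5.6 cases per parameter, outside it. A joint five-mediator model already has 10 + 5 + 2 + 6 = 23 before any covariate.

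**The case against.** A reader might infer that the protocol confines adjustment to Aim 1 and will run Aim 2 unadjusted. The text does not say so. The main-effects sentence does not exclude Aim 2, and two sections leave covariates open for the analyses in general. Aim 2 itself names gender, initial insomnia and fatigue severity, and inflammation as moderators, and models with such interactions would ordinarily carry their main effects. The path model is that of Fig. 1, which is not shown. A fully specified analysis plan is promised before unmasking. All of this stands against any claim that adjustment is ruled out. It does not turn an option into a commitment for the mediator-to-outcome path. Health Report data, moreover, are gathered during the intervention and follow-up, so they are not baseline covariates.

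The Background sentence says that dyspnea and inflammation affect insomnia, not that they cause the mediators, and its third item, emotional arousal, is itself a hypothesised mediator. That is correct. The link to the mediators comes from elsewhere: the Background ties anxiety and depressed mood to the disease, and the COPD self-efficacy scale asks about managing breathing. It is plausible rather than demonstrated. No timing is given for the CRQ dyspnea scale, so it should not be assumed to be a baseline measure.

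Analysing change removes stable causes that only shift levels. This is true, but correlated baselines still induce correlated changes, as step 4 shows.

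Finally, covariate lists commonly belong in the analysis plan. That is fair for the detail. The point here rests on what the article does fix: an association between two changes, read as mechanism, with measurement error as the only stated limitation.

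**Conclusion.** The point holds in a limited form. The protocol gives Aim 2 a causal reading, commits its baseline adjustment to the main-effect analyses, and states no confounder set, no-confounding assumption or sensitivity analysis for the mediator-to-outcome path. It does not state that Aim 2 will be unadjusted.

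The rates of about 18%, 55% and 80% are illustrations. The residual correlations, the 0.5 SD mediator shift, the 0.5 SD total effect, and the baseline and pre-to-post correlations are all assumptions, and none comes from the document. They show that modest shared causes matter at N = 140, not how large such causes are in this population. Baseline adjustment reduces the problem but does not abolish it: partly measured causes leave a remainder, and post-baseline causes such as an exacerbation during treatment are untouched. Aim 1 is not affected. The change is worth making because it uses data already collected and fits the sponsor's own limit on model size.

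**What to change.** In the Aim 2 paragraph:

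1. State that mediators are modelled one at a time, and that both the mediator and the outcome equation include the baseline mediator, the baseline outcome and one prespecified prerandomisation severity measure already collected, for example screening pulmonary function. This gives 13 parameters.
2. Beside each indirect effect, report the residual mediator–outcome correlation at which it would become null. In this linear model, that is the correlation between the residuals of the mediator and of the outcome after both are regressed on the components and the baseline covariates.
3. Describe indirect effects as conditional on no remaining mediator–outcome confounding, and list this beside measurement error as a limitation.

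The cost is protocol or analysis-plan wording and Mplus code, with no new data. The downside is a few more coefficients per model, and some indirect effects will look smaller. A much longer covariate list is not advised, because it would exceed the protocol's cases-per-parameter convention.

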#### Missing data

For missing data, we will determine whether missing data are MCAR (missing completely at random), MAR (missing at random), or NMAR (not missing at random). If MCAR or MAR, the standard multivariate computations will not likely result in biased standard error estimates, and full information maximum likelihood (FIML) estimation will be used. If NMAR, we will use the “pattern mixture” approach to compute a “weighted average” of the parameters associated with the missing data to estimate treatment effects.

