#### Power analysis

Power analysis for aim 1 is based on main effect differences at the end of the intervention. We estimated the per cell sample size assuming a moderate effect size (Cohen’s *d* = 0.5), alpha = 0.05, and power = 0.80 using the fpower SAS macro available at http://www.datavis.ca/sasmac/fpower.html. Based on combined data from our pilot study measures, the minimum detectable difference (MDD) for the treatment main effects will be clinically meaningful. For example, we will be able to detect a 2.3-point difference in insomnia severity between those receiving COPD-ED versus those not, averaged across the other treatment conditions. The MDD for other outcomes includes Actiwatch® sleep efficiency = 6.72, CRQ-F = 0.51, and the Profile of Moods States Fatigue subscale (POMS-F) = 2.76. Between-group effect size estimates from our pilot study ranged from 0.35 for sleep efficiency to 1.03 for insomnia severity, comparing the proposed treatment components. Path models using 7–14 parameters can be estimated according to the sample size convention of 10 to 20 cases per parameter [61], thus, our simple path models can be estimated. We further conservatively estimate an attrition rate of 15 % by the end of the study. Therefore, we will enroll a total of 166 and retain 140 (35 per group) subjects in the proposed study.

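### The missing-data rule lets the main estimator depend on telling MAR from NMAR, which observed data cannot do; fix the MAR analysis as primary and always run an NMAR sensitivity analysis

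*Protocol article*

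**What the plan says.** The Missing data section sets a rule in two steps. First, "we will determine whether missing data are MCAR (missing completely at random), MAR (missing at random), or NMAR (not missing at random". No criterion for that decision is given. Second, the estimator follows from the answer. Under MCAR or MAR, "full information maximum likelihood (FIML) estimation will be used". Otherwise the effects come from a different model: "If NMAR, we will use the “pattern mixture” approach to compute a “weighted average” of the parameters associated with the missing data to estimate treatment". Pattern mixture is therefore a conditional replacement for the likelihood estimate, not an analysis reported beside it.

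Other places bear on the rule:
- Test of specific hypotheses, Aim 1: the mixed models are "estimated by residual maximum likelihood (REML").
- Test of specific hypotheses, opening paragraph: "Necessary transformation and imputations are conducted based on the raw data distribution". The same paragraph promises intention-to-treat analysis and a full SAP before unmasking.
- Power analysis: "We further conservatively estimate an attrition rate of 15 % by the end of the study".
- Data collection: reasons for non-completion are recorded to support the assumptions made about missing data, and analysis staff are blinded to group.

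**The concern.** MAR and NMAR differ only in how the unobserved outcomes behave, given everything observed. A rule that first decides between them asks the data a question they cannot answer. More detail in the SAP would not help, because an SAP that follows this rule inherits the same undecidable step. The problem lies in what the protocol fixes, not in what it leaves out.

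Two consequences follow. If the team settles on MAR, nothing in the rule calls for a look at departures from MAR. If the team settles on NMAR, the headline estimate moves to a different model on a judgement that cannot be checked. Informative dropout is a fair worry in this trial: the Background section itself says that exacerbations may interfere with CBT-I outcomes.

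**Working it through.** **1. Reproduce the plan's figure.** The Power analysis section states "we will enroll a total of 166 and retain 140 (35 per group) subjects in the proposed study". At 15% attrition, 140 / 0.85 = 164.7, which rounds up to 165, against 166 stated. The figure reproduces to within one participant. Planned loss is 166 − 140 = 26, and 26 / 166 = 0.1566, or 15.7%. This is loss by the end of the study. The article gives no figure for the end of the intervention (T2) and none by arm.

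**2. What the data can and cannot show.** The joint distribution splits into (observed values and missingness pattern) × (unobserved outcomes, given observed values and pattern). The data inform only the first factor. MCAR restricts that factor, for example by requiring dropout to be unrelated to baseline, so the data can contradict it. MAR says that, given the observed values, unobserved outcomes are distributed like observed ones. NMAR says they are not. That statement concerns only the second factor.

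A simulation of 2,000 trials with N = 166 illustrates this, under assumed mechanisms. The outcome is 0.5 × baseline + 0.5 × arm + noise (variance 0.75), with standard normal baseline. The log-odds of dropout are −2.0 + 0.6 × baseline (MAR) or −1.9 − 0.7 × (outcome − 0.25) (NMAR). A logistic regression of dropout on baseline and arm, at the 5% level, flagged dependence in 70.5% of MAR trials (13.3% missing) and 37.9% of NMAR trials (15.0% missing). The check detects departure from MCAR. It does not identify NMAR, and here it fired more often under MAR.

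**3. How far the estimate could move.** Let m be the share missing and s the number of SII points by which missing outcomes are worse than MAR predicts. Then:

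fall in effect = m(treated) × s(treated) − m(control) × s(control)

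The shifts are assumptions. The upper value of 6 borrows the meaningful change on the SII given under Outcomes, Insomnia.

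| Missing, treated / control | Shift, treated / control | Fall in effect (SII points) |
|---|---|---|
| 15.7% / 15.7% | 0 / 0 | 0 |
| 15.7% / 15.7% | 3 / 0 | 0.157 × 3 = 0.47 |
| 15.7% / 15.7% | 6 / 0 | 0.157 × 6 = 0.94 |
| 15.7% / 15.7% | 6 / 6 | 0.94 − 0.94 = 0 |
| 20% / 10% (assumed split) | 6 / 6 | 1.20 − 0.60 = 0.60 |
| 10% / 20% (assumed split) | 6 / 6 | 0.60 − 1.20 = −0.60 (effect grows) |

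For a given split of missingness, changing the shifts leaves the observed data unchanged, so no test on those data can choose among the shifts.

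**The case against.** The strongest reply is that the article never says the classification will come from a statistical test. Read with the Data collection section, it can mean a reasoned judgement based on recorded reasons for dropout. That stands as far as it goes: the judgement can be made, so it would be too strong to say the branch cannot be carried out. But recorded reasons make NMAR more or less plausible without establishing it. They suit the choice of shifts in a sensitivity analysis better than a switch between estimators.

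Exacerbations and corticosteroid use are also monitored and may serve as covariates (Clinical assessment). Dropout that these explain can be partly handled under MAR. This reduces the likely bias but does not remove the problem with the rule.

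Three stronger readings are tempting, and the article does not support them.
- *The estimator will be picked by its result.* Analysts are blinded to group and the SAP is to precede unmasking. Both limit such selection, though neither makes MAR distinguishable from NMAR, and neither helps if the NMAR analysis is never run.
- *REML and FIML are competing ways of handling missing data.* Both are likelihood methods valid under MAR and can coexist; FIML fits naturally with the Aim 2 path models. The sentence on imputation is loose, but it follows one on data screening and its detail can be left to the SAP.
- *The bias could consume 41% of the detectable difference (0.94 / 2.3).* The 2.3 points refer to the end of the intervention and the 15% to the end of the study, so the ratio mixes time points. It also assumes a shift in treated participants only. If 2.3 points corresponds to d = 0.5, the SD is 2.3 / 0.5 = 4.6, and a mean shift of 6 points is 6 / 4.6 = 1.3 SD, which is severe.

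**Conclusion.** The point holds. The rule makes the main estimator depend on a classification that observed data cannot settle. It leaves departures from MAR unexamined in one branch and changes the main estimate on an unverifiable judgement in the other. The existing safeguards narrow the room for abuse but do not repair the rule.

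The size cannot be fixed from the article. The range of 0 to 0.94 SII points rests on up to 15.7% missing equally at both levels of a component, no shift in missing controls, and a shift of 0 to 6 points in missing treated participants. Equal shifts with equal missingness give no bias, and unequal dropout can push the estimate either way. This is a correction that should be made to the analysis plan; it does not undermine the design or the sample size.

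**What to change.** Delete the branch in the Missing data section and state instead:

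- The primary Aim 1 analysis is, in every case, the likelihood-based mixed model on all randomised participants, valid under MAR.
- A prespecified pattern-mixture sensitivity analysis, delta-adjusted or as a tipping point, is always reported for each component, whatever any check on missingness shows.
- Shifts are set on each outcome's own scale, since SII points do not carry over to actigraphy, CRQ-F or PROMIS fatigue. Their plausibility is judged from the recorded reasons for dropout.

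The grid of shifts and the time points can be left to the SAP. The protocol already names both methods, the trial is still recruiting, and the SAP is yet to be written, so the change can be made cleanly now. It costs wording and modest extra programming, with no new data or participants.
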